#### Clinical data analysis

2.11.2

All randomized participants will be included in the preliminary analysis according to the intention-to-treat (ITT) principle. Data will be analyzed with SPSS v25.0 (IBM, Armonk, NY, USA). A two-tailed *p*-value of ≤ 0.05 will be taken to indicate statistical significance, and continuous data will be reported as mean ± standard deviation (SD). For normally distributed continuous variables, an independent-samples *t*-test will be used, whereas for non-normally distributed data, the Mann–Whitney *U* test will be applied. Categorical and ordinal variables will be expressed as percentages (%) and analyzed using the chi-square test when expected cell counts are adequate (typically all expected counts ≥5), or Fisher's exact test when expected counts are small. Ordinal data will be analyzed using the rank-sum test.

The incidence of adverse events will be summarized in the safety analysis and compared between groups using the chi-square test or Fisher's exact test, as appropriate. Missing data for participants who withdraw or deviate from the protocol will be handled using listwise deletion or multiple imputation methods.

fMRI data will be analyzed by experienced imaging specialists. All statistical analyses will be performed by independent data analysts who are blinded to group allocation, thereby minimizing potential bias.

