**Figure 1 F1:**
[figure not shown]
Flow chart of the clinical trial procedures.

The trial has been prospectively registered in the Chinese Clinical Trial Registry (ChiCTR2400086748) on 10 July 2024. The trial registration was updated on 30 October 2025 to clarify the outcome hierarchy (rs-fMRI/DTI as the primary outcome; SSA/VFSS-based measures/MoCA/SWAL-QOL as secondary). No other changes were made.

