#### Secondary outcomes: mean changes in SSA, VFSS-based measures (MBSImP and PAS), MoCA, and SWAL-QOL scores during the study period

2.7.3

(1) SSA (Standardized Swallowing Assessment): The SSA consists of three components: clinical examination, 5 ml and 60 ml water swallowing tests (25). Higher scores reflect more severe swallowing dysfunction. Existing evidence suggests that the SSA offers good sensitivity and specificity when used to assess PSD patients (26).

(2) VFSS (Video fluoroscopic Swallowing Study)-based measures: VFSS is considered one of the most accurate methods for the diagnosis of dysphagia and is conducted using X-ray fluoroscopy to evaluate the transit of food boluses with contrast agent from the oral cavity to the esophagus in both anteroposterior and lateral views (27). Swallowing impairment will be quantified using the Modified Barium Swallow Impairment Profile (MBSImP), which scores standardized physiologic components observed on VFSS across the oral and pharyngeal phases, including pharyngoesophageal segment opening, and also incorporates upright esophageal clearance as a screening component, using ordinal impairment ratings (0 = normal; higher scores = more severe impairment), thereby generating a profile-based characterization of swallowing dysfunction (28). Because airway invasion is a critical safety dimension, penetration/aspiration events during VFSS will additionally be graded using the Penetration–Aspiration Scale (PAS), an 8-point ordinal scale in which PAS = 1 indicates no airway entry and higher scores indicate increasing penetration/aspiration severity (29). MBSImP (with PAS as a complementary safety indicator), together with SSA, will enable a comprehensive evaluation of swallowing function and therapeutic response in PSD.

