(3) MoCA (Montreal Cognitive Assessment): In traditional Chinese medicine, “Spirit” refers to the sum of vital activities and mental processes, including cognition, perception, and emotion. Cognitive function is therefore considered part of “Spirit” and reflects its regulatory capacity, which also influences cerebral function (30). Patients with PSD frequently present with concomitant cognitive impairment (31). The MoCA serves as a widely adopted tool for cognitive evaluation with strong reliability and validity (32). It assesses eight domains: attention, orientation, fluency, naming, visuospatial skills, abstraction, delayed recall, and sentence repetition. The total score is 30, with one additional point added for individuals with fewer than 12 years of education. A lower score indicates greater cognitive impairment. It will be used to quantify changes in cognitive function attributable to acupuncture.

(4) SWAL-QOL (Swallowing Quality-of-Life Questionnaire): The SWAL-QOL comprises 44 items covering appetite, mealtime duration, food selection, sleep, and psychological status, and is specifically developed to measure the quality of life of individuals with PSD (33). A higher score corresponds to better quality of life. It will be employed to evaluate the impact of acupuncture on patients' quality of life.

Assessment schedule: baseline (week 0), weeks 2 and 4, and week 6 (end-of-treatment). All assessments will be performed by trained, blinded evaluators.

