Statistical Modeling: For clinical outcomes and imaging metrics, linear mixed-effects models will be employed to assess within-subject change (baseline vs. week 6) and between-group differences (acupuncture vs. control), while adjusting for sex, age, stroke severity, and lesion volume (48). Correlation analyses will test associations between rs-fMRI/DTI metrics and clinical improvement in swallowing function (SSA/VFSS-based measures/MoCA/SWAL-QOL scales) (49, 50). This will aid in assessing whether alterations in brain networks correlate with improvements in swallowing function, thereby enhancing the clinical interpretability of imaging findings. Depending on the assumptions of normality and linearity, analyses will use either Pearson's correlation coefficient or Spearman's rank correlation coefficient.

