**Figure 3 F3:**
[figure not shown]
SPIRIT schedule of enrolment, interventions, and assessments. EOT, End of Treatment; rs-fMRI/DTI at baseline (t0), and Week 6; SSA at t0/Weeks 2/4/6; VFSS/MoCA/SWAL-QOL at t0 and Week 6; AEs monitored throughout.

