## Conclusions

4

In conclusion, this randomized controlled trial employing rs-fMRI and DTI is designed to assess both the clinical efficacy and the central neural mechanisms of Tiao Shen Li Yan acupuncture in PSD. The results are expected to provide objective evidence regarding the clinical efficacy and neural mechanisms of acupuncture and to serve as a valuable reference for evidence-based PSD management guidelines.

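### The trial expects to give evidence of clinical efficacy, but its five clinical scores are unordered secondary outcomes, each judged at 0.05 with no multiplicity control

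*Protocol article*

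**What the plan says.** **Outcomes.** Section 2.7.3 of the protocol article defines the secondary outcomes as "mean changes in SSA, VFSS-based measures (MBSImP and PAS), MoCA, and SWAL-QOL scores during the study period". That is four instruments, or five scores when the two VFSS-based measures are counted separately. None is named as the lead. Section 2.1 reports a registry update on the outcome hierarchy: "rs-fMRI/DTI as the primary outcome; SSA/VFSS-based measures/MoCA/SWAL-QOL as secondary". It ranks imaging above the clinical scales but sets no order among the scales.

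**Decision rule.** Section 2.11.2 says, for clinical data, that a two-tailed p-value "≤ 0.05 will be taken to indicate statistical significance". The only corrections described, in section 2.11.1, are FDR at voxel level and Bonferroni at network level. Both are for imaging.

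**Visits.** Section 2.11.1, which covers clinical outcomes as well as imaging metrics, says that "linear mixed-effects models will be employed to assess within-subject change (baseline vs. week 6"), together with the between-group difference. The legend to Figure 3 reads "SSA at t0/Weeks 2/4/6; VFSS/MoCA/SWAL-QOL at t0 and Week 6". Section 2.7.3 is looser and does not split visits by scale: "Assessment schedule: baseline (week 0), weeks 2 and 4, and week 6 (end-of-treatment").

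**Conclusion to be drawn.** Section 4 says the trial "is designed to assess both the clinical efficacy and the central neural mechanisms of Tiao Shen Li Yan acupuncture in PSD" and adds: "The results are expected to provide objective evidence regarding the clinical efficacy and neural mechanisms of acupuncture". The Introduction and section 2.1 also give efficacy as an aim.

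**The concern.** The article states both a decision rule and the conclusion it is meant to serve, and the two do not fit. Under the rule, a nominally significant difference on any one of five scores counts as significant. Nothing says which score an efficacy statement must rest on. A single result on cognition or quality of life, with nothing on swallowing, could therefore be reported as clinical efficacy, and a reader would give it the error rate of one planned test.

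The imaging side is treated differently. The article describes its multiplicity control, and the Discussion separates primary from supportive imaging analyses. The clinical side has no counterpart, although section 4 offers the results as a reference for management guidelines.

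**Working it through.** The article states no error rate for the clinical scores, so there is no figure to reproduce. The check asks what the stated rule implies if acupuncture has no effect on any score.

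**Inputs from the article**
- Level: 0.05, two-tailed, per test (section 2.11.2). In the direction favouring acupuncture this is 0.025.
- Number of tests, k: 5 scores, or 4 instruments if VFSS counts once (section 2.7.3).
- Contrast: change from baseline to week 6, one test per score (section 2.11.1; Figure 3 legend).
- Group size: 20 per arm evaluable, 23 per arm randomised (sections 2.1 and 2.9).

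**Assumption**
- The article gives no correlation between scores. A common correlation r of 0, 0.3, 0.5 and 0.7 is shown. Scores are signed so that positive favours acupuncture.

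**Independent tests**
- Either direction: 1 − (1 − 0.05)^k
  - k = 5: 1 − 0.95^5 = 22.6%
  - k = 4: 1 − 0.95^4 = 18.5%
- Favouring acupuncture: 1 − (1 − 0.025)^k
  - k = 5: 1 − 0.975^5 = 11.9%
  - k = 4: 1 − 0.975^4 = 9.6%

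**Correlated tests** (equicorrelated multivariate normal, one million draws per setting; the r = 0 row is from the formulas above)

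| r | k = 5, either direction | k = 5, favouring acupuncture | k = 4, either direction | k = 4, favouring acupuncture |
|---|---|---|---|---|
| 0 | 22.6% | 11.9% | 18.5% | 9.6% |
| 0.3 | 20.9% | 10.5% | 17.4% | 8.7% |
| 0.5 | 18.3% | 9.1% | 15.6% | 7.8% |
| 0.7 | 14.9% | 7.5% | 13.1% | 6.6% |

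**Small-sample check.** Simulated two-sample t-tests agree. For k = 5 and r = 0.5 they give 18.5% and 9.1% with 20 per arm, and 18.6% and 9.2% with 23 per arm.

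**Relative size.** For five scores, a false result favouring acupuncture is 7.5 / 2.5 = 3.0 to 11.9 / 2.5 = 4.8 times as likely as with one planned test.

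**After the fix.** With one named outcome at one visit, the rates return to 5.0% in either direction and 2.5% favouring acupuncture.

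**The case against.** The strongest reply has three parts.

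1. Section 2.9 describes the whole study, not only its imaging, as exploratory, and the clinical scales are all secondary. Unadjusted secondary outcomes are common in a 46-patient trial of this kind. The limitations paragraph admits the small sample and calls for larger trials.
2. Order and adjustment among secondary outcomes are details usually left to a statistical analysis plan.
3. No passage says that one significant scale establishes efficacy, or calls the clinical tests confirmatory.

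The first part stands as a limit on severity, and it makes formal adjustment of every scale debatable. It does not remove the point, because no passage calls the clinical p-values descriptive and section 4 still expects evidence of efficacy. The second part would hold if the article were merely silent. Here it states the threshold and the intended conclusion, and the threshold does not carry the conclusion. The third part is correct and is why the point is framed as a mismatch between rule and wording.

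A reader might infer three stronger things that the document does not support.

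- **That the 18% to 23% range is the chance of a false efficacy claim.** Those either-direction rates also count results favouring sham. The relevant rate is about half as large.
- **That no visit is fixed.** Section 2.11.1 gives baseline against week 6, and by the Figure 3 legend week 6 is the only post-baseline visit for every scale except SSA.
- **That seven tests are planned, with SSA tested at weeks 2, 4 and 6.** No passage states tests of SSA at weeks 2 and 4. Likewise, MBSImP components are scored, but separate tests of them are not stated.

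Counting five efficacy tests can also be questioned, since section 2.7.3 presents PAS as a safety complement to MBSImP. The four-instrument columns cover that reading.

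**Conclusion.** The point holds and should be fixed, but it does not undermine the trial. With five week-6 tests and no true effect, at least one false significant difference in either direction has probability 22.6% under independence, and about 15% to 21% at correlations of 0.7 to 0.3. At least one false result favouring acupuncture has probability about 7.5% to 12%, against a nominal 2.5%. With four instruments the ranges are about 13% to 18.5% and 6.6% to 9.6%.

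These figures assume one test per score, each holding its nominal level, and a common correlation that the article does not supply. Since SSA, MBSImP, PAS and SWAL-QOL all concern swallowing, the independence figures are best read as upper values.

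A smaller matter goes with it. The visit statements in section 2.7.3 are looser than those in section 2.11.1 and the Figure 3 legend, so what SSA at weeks 2 and 4 is for remains unclear.

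**What to change.** Before unblinding, add to section 2.11.2 that one swallowing outcome at week 6 is the key clinical secondary, and that any statement on clinical efficacy rests on it. SSA change from baseline is one candidate, being the only scale that the Figure 3 legend places at every visit. Report the other scales, and SSA at weeks 2 and 4, as supportive with estimates and 95% confidence intervals. Bring the visit wording in section 2.7.3 into line with section 2.11.1 and the Figure 3 legend.

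Alternatively, label all clinical secondaries exploratory and reword section 2.1 and the Conclusions, with the matching aim in the Introduction, so that no clinical-efficacy conclusion is drawn from them.

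Either route costs a few sentences and no new data. Section 2.15 reports that at submission the data were still blinded and no primary outcome analysis had been done; the change is credible only if that is still so when it is made. The price is that an isolated nominal result on another scale can no longer be presented as evidence of efficacy.

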### Registration and trial design

2.1

This single-blind, randomized, sham-controlled trial aims to investigate the therapeutic efficacy and neural mechanisms of Tiao Shen Li Yan acupuncture in patients with PSD.

Forty-six participants will be randomized in a 1:1 ratio to receive Tiao Shen Li Yan acupuncture or sham acupuncture. An additional cohort of healthy volunteers will undergo baseline rs-fMRI and DTI for reference comparisons. Participants will be included only if they fulfill all eligibility criteria and submit written informed consent. Figure 1 shows the research process for this article.

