### Eligibility criteria

2.3

**Inclusion criteria:** (1) ischemic stroke and dysphagia diagnosed per accepted criteria (15, 16), with Kubota Water Swallowing Test (WST) ≥grade II; (2) aged 30–80 years; (3) stroke onset 2 weeks to 6 months prior; (4) conscious, hemodynamically stable, and able to comply with procedures; (5) written informed consent.

**Exclusion criteria:** (1) coma, Parkinson's disease, or Alzheimer's disease (AD); (2) Severe cardiac, renal, or other organ failure, or critically ill stroke with unstable vital signs. (3) failure to meet the diagnostic criteria for PSD or absence of cerebrovascular disease on neuroimaging; (4) inability to cooperate with evaluation or treatment, or poor adherence; (5) severe psychiatric disorders precluding cooperation with observation or treatment; and (6) contraindications to MRI (e.g., ferromagnetic implants).

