### Adverse events and safety monitoring

2.12

All adverse events (AEs) will be recorded in the case report form (CRF) and managed within 24 hours. A study physician will evaluate each AE and document AE type, onset/duration, management, outcome, CTCAE grade (1–5), and causality (definitely/probably/possibly/unlikely/unrelated).

AEs will be graded according to the Common Terminology Criteria for Adverse Events (CTCAE): Grade 1 (mild), Grade 2 (moderate), Grade 3 (severe), Grade 4 (life-threatening), and Grade 5 (death). Serious adverse events (SAEs) (fatal, life-threatening, requiring/prolonging hospitalization, or causing persistent/significant disability) and emergencies will be reported to the ethics committee and relevant institutional personnel within 24 hours of awareness.

Participants may withdraw at any time; investigators may discontinue the intervention if continuation is deemed unsafe. Participants experiencing AEs will be followed until stabilization/resolution. The principal investigator will review AE reports regularly, and a safety review meeting will be convened if necessary. Potential acupuncture-related AEs include syncope, needle retention/breakage, local hematoma, and localized infection; participants with severe intervention-related AEs will be withdrawn immediately.

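### Section 2.11.2 promises intention-to-treat but allows listwise deletion, unranked against multiple imputation, for missing data of patients who withdraw or deviate

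*Protocol article*

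**What the plan says.** Section 2.11.2 (Clinical data analysis) opens with the analysis population: "All randomized participants will be included in the preliminary analysis according to the intention-to-treat (ITT) principle". No other analysis set is defined. The section then lists two-sample tests: "For normally distributed continuous variables, an independent-samples *t*-test will be used", with Mann–Whitney and rank-sum tests for non-normal and ordinal data. Its last statement on incomplete data is "Missing data for participants who withdraw or deviate from the protocol will be handled using listwise deletion or multiple imputation methods". It does not say which method is primary, which outcomes each applies to, or what decides between them.

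Section 2.11.1 also names a model for the same clinical outcomes, in a sentence that starts "For clinical outcomes and imaging metrics, linear mixed-effects models will be employed to assess within-subject change (baseline vs. week 6". That sentence goes on to between-group differences, adjusted for sex, age, stroke severity and lesion volume.

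Section 2.9 expects 15% dropout. The caption of Figure 3 puts SSA at baseline and weeks 2, 4 and 6, and VFSS, MoCA, SWAL-QOL and imaging at baseline and week 6 only.

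**The concern.** Two statements in one section cannot both hold once a value is missing. Listwise deletion removes the patient from the comparison, so the analysis no longer contains everyone randomised. What remains compares completers, and the protection that randomisation gives extends to them only if the loss is unrelated to prognosis or to arm.

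The rule is also open. Either method satisfies the text, so the choice can be made once the extent and pattern of missing data are visible. This is a rule the article states, not a detail it leaves out, and one of its two branches is incompatible with the property claimed a few lines above.

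SSA makes the loss concrete. A patient who leaves after week 4 has a baseline and two post-baseline SSA scores. Deletion discards them; a model or an imputation can use them.

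**Working it through.** **1. The plan's own figure.** Section 2.9 starts from 20 per group, 40 in total, and adds 15%: 40 × (1 + 0.15) = 46. This reproduces exactly.

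**2. What deletion removes.** Inputs are 46 randomised (section 2.1: "Forty-six participants will be randomized in a 1:1 ratio to receive Tiao Shen Li Yan acupuncture or sham acupuncture") and 15% dropout (section 2.9).
- Removed: 46 × 0.15 = 6.9, about 7 patients.
- Remaining: 46 × 0.85 = 39.1, about 39 patients, or 23 × 0.85 = 19.55 per arm if both allocation and loss are even.

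So under deletion the intention-to-treat sentence fails for about 15% of those randomised.

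**3. Each method against the promise.**

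| Method | All randomised kept? | SSA at weeks 2 and 4 used for a patient missing week 6? |
|---|---|---|
| Listwise deletion with the section 2.11.2 tests | No | No |
| Multiple imputation | Yes | Yes, if in the imputation model |
| Mixed model of section 2.11.1 | Yes, if baseline is one of the responses | Yes, if those visits are included |

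The mixed model as written compares baseline with week 6, so using the interim SSA visits needs a stated extension. For outcomes measured only at baseline and week 6, a patient without week 6 contributes only a baseline value.

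**4. When deletion biases the comparison.** Let f be the fraction lost in an arm and k the amount, in SD, by which its dropouts do worse than its completers. The arm's full mean is the completer mean minus f·k, so the completer mean is too favourable by f·k. With the same k in both arms and no true effect:

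bias = k × (f_active − f_sham)

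The document gives neither k nor dropout by arm. Assuming 23 per arm and k of 0.5 to 1.0:

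| Dropouts, active vs sham | f_active − f_sham | Bias (SD) |
|---|---|---|
| 3 vs 3 | 0 | 0 |
| 5 vs 2 | 3/23 = 0.130 | 0.07 to 0.13 |
| 6 vs 1 | 5/23 = 0.217 | 0.11 to 0.22 |
| 7 vs 0 | 7/23 = 0.304 | 0.15 to 0.30 |

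The table shows only how the answer depends on its assumptions. It runs from nothing to about 0.3 SD, and nothing in the document selects a row. For scale, the standard error of a standardised difference at 19.55 per arm is √(2/19.55) = 0.32.

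**The case against.** The case on the other side is substantial. Multiple imputation is offered in the same sentence and keeps everyone, so the plan permits a completer analysis without fixing one. The mixed model is already planned for the clinical outcomes. The rule sits in the clinical section, which covers secondary endpoints; the primary outcomes are imaging metrics. Analysts are blinded to allocation and unblinding follows database lock and the primary analyses, which limits an outcome-driven choice of method. The trial calls itself exploratory, and ranking missing-data methods is often left to an analysis plan. All of this reduces the seriousness. It does not reconcile the promise with the deletion option, since the article itself chose to name both.

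Four stronger readings are tempting and should not be drawn.

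- **That the plan sets up a per-protocol analysis.** The sentence concerns missing data. It does not say that deviators with observed outcomes are removed, and no per-protocol set is defined. Naming deviators is unclear, because deviating does not itself make a value missing, but that calls for clarification only.
- **That patients are excluded after randomisation for non-adherence.** The criterion "inability to cooperate with evaluation or treatment, or poor adherence" is in the eligibility list of section 2.3 and reads as a judgement at entry. No section provides for later exclusion on this ground.
- **That arm-specific loss is established.** Section 2.12 says "participants with severe intervention-related AEs will be withdrawn immediately", and only the active arm has penetrating and bleeding needling, so unequal loss is possible. The document gives no dropout by arm.
- **That the fix removes a bias of 0.08 to 0.27 SD.** The upper figure is φ(z) at the 15% point over 0.85, 0.233/0.85 = 0.274. The lower range multiplies it by assumed correlations of 0.3 and 0.5 (0.082 and 0.137). Both need outcome-related loss in one arm and unrelated loss in the other; the bias is zero if dropout is the same in both. Loss of that kind is missing not at random, which neither the mixed model nor standard multiple imputation would fully remove.

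**Conclusion.** The point holds as a conflict between a stated property and a stated rule. Section 2.11.2 claims intention-to-treat for all randomised patients and leaves open a method that breaks it. If that method is used at the planned 15% dropout, about 7 of 46 patients leave the clinical comparison, it becomes a completer analysis, and interim SSA data are lost.

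The breach of intention-to-treat follows whenever data are missing and deletion is chosen. Bias does not follow automatically: it needs dropout related to both arm and outcome, and its size cannot be derived from the document. The count of 7 rests only on the article's own dropout figure.

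**What to change.** In section 2.11.2:

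1. Delete listwise deletion as a primary option.
2. Make the mixed-effects model of section 2.11.1 the primary analysis of the clinical outcomes, on all randomised participants as allocated. Treat baseline as one of the responses, and use every observed value, including SSA at weeks 2 and 4 and any values recorded after a deviation or after treatment stops.
3. Name multiple imputation as a sensitivity analysis. Its model should contain arm, baseline, the adjustment covariates and, for SSA, the week 2 and week 4 scores.
4. Keep complete-case analysis, labelled as supplementary only.
5. Because the methods in 2 and 3 assume missing at random, add a simple delta-shift analysis: worsen the imputed week-6 values by a range of amounts, including different amounts by arm, and report where the conclusion changes.

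The cost is a change of wording and a little more analysis work; no patients, visits or measurements are added. Section 2.15 reports that, at submission, data were still blinded and no primary outcome analyses had been done. The change should be dated before unblinding. If unblinding has already happened, it should be reported as made afterwards.
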